**Methods:**

A parallel-group, single-blinded, severity-stratified, randomized clinical trial will test the superiority of BMT over enhanced usual care. Eligible participants will be those seeking treatment and who fulfill DSM-V criteria for alcohol use disorder and criteria for harmful alcohol use. With an estimated a loss to follow-up of 20%, a total of 182 participants will be recruited and equally randomized to each treatment group. The intervention group will receive an adaptation of the motivational enhancement therapy, as manualized in Project MATCH. This treatment consists of four 45-min sessions provided by a general psychologist with at least 3 years of primary care experience. The primary outcome is the change from baseline in the drinks per drinking day during the last 90 days, which will be captured using the Timeline Follow Back method. Secondary outcomes will describe the changes in alcohol use pattern, motivational status, and severity of the disorder.

All participants will be analyzed according to the group they were allocated, regardless of the treatment actually received. Mean differences (MD) will be computed for continuous outcomes and relative risks (RR) and RR reductions (RRR) for dichotomous results. Linear models will deliver the subgroup analyses. Missingness is assumed to be associated with the baseline alcohol use pattern and severity, so a multiple imputation method will be used to handle missing data.

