### Participant timeline {13}

### Sample size {14}

Given that there is a spontaneous reduction of alcohol consumption in control groups of 14% [26], and that the reduction attributed to psychosocial treatments in the literature is around 40% [27], we set a superiority margin δ of 26% reduction in alcohol consumption. The following two hypotheses correspond to the superiority test:
H_0_: DDD_EUC_ − DDD_BMT_ = < δ;H_a_: DDD_EUC_ − DDD_BMT_ > δ.

We used local data and the results of project MATCH as references for sample size calculation. Project MATCH [13] recruited participants with AUD in the outpatient setting and observed a standard deviation (SD) of 6.29 drinks, which is similar to reports in Chilean PC [28]. On admission, participants in the MATCH study consumed 11.5 DDD, which should be similar in our population. We expect a decrease of 14% in the EUC group [26], that is, to 9.89 DDD, and a reduction to 40% in the intervention group [27, 29], that is, a decrease to 6.9 DDD.

The sample size was obtained using the formula for means comparison in superiority studies of parallel groups, according to the methodology described by Chow [30]. The computation was made using the R statistical software [31] with the package provided by the same author [30, 32]. We obtained a sample size of *n*_1_ = *n*_2_ = 76 using the following parameters: *α* = 0.05; *β* = 0.2 : *σ* = 6.29; *δ* = 2.99; *κ* = 1 (where *α* is the type 1 error, [1- *β*] the power, *σ* the standard deviation, *δ* the expected difference between both groups, and *κ* the allocation ratio between both groups).

Considering an expected loss to follow-up of 20%, we will have to recruit 91 participants for each group, which is 182 participants in total.

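### The 76 per group does not follow from the stated inputs under the named superiority formula, and 91 per group at 20% loss leaves about 73, not 76

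*Protocol article*

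**What the plan says.** All inputs are in the protocol article under Sample size {14}. The baseline is 11.5 drinks per drinking day. A 14% fall is expected under enhanced usual care (to 9.89) and a 40% fall under the brief motivational treatment (to 6.9). The SD is 6.29 and allocation is 1:1. The section gives α as 0.05 and β as 0.2, and explains the symbols: "where *α* is the type 1 error, [1- *β*] the power". It cites a textbook formula for comparing means in superiority studies and reports 76 per group ("76 using the following parameters"). In that parameter list δ is 2.99 and is described as "δ* the expected difference between both groups".

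Earlier in the same section δ is the superiority margin, set at a 26% reduction. It stands in both hypotheses, which are introduced with "The following two hypotheses correspond to the superiority test": the null is a difference of at most δ and the alternative a difference above δ. Whether α is one- or two-sided is not stated.

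For an expected 20% loss to follow-up, "we will have to recruit 91 participants for each group, which is 182 participants in total". The abstract repeats the 20% loss and the total: "a total of 182 participants will be recruited and equally randomized to each treatment group".

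**The concern.** The article prints the inputs and the result, so a reader can put one into the other, and they do not agree. Nothing is alleged to be missing; the printed figures conflict. There are two separate steps:

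- from the inputs to 76 per group;
- from 76 to 91 per group after allowing for loss.

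At stake is whether 182 is justified by the calculation offered for it, and whether the trial keeps the power it claims. A reader cannot tell from the section which sidedness, which β and which null value the trial was sized for.

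**Working it through.** **Inputs** (Sample size {14}): α = 0.05, β = 0.2, σ = 6.29, 1:1 allocation, 20% loss. Expected difference: 11.5 × 0.86 − 11.5 × 0.60 = 9.89 − 6.90 = 2.99. Margin: 26% of 11.5 = 2.99, the same number.

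**Step 1: the number per group for a zero-difference null.** The formula is n = 2σ²(z_α + z_β)² / δ², and 2 × (6.29/2.99)² = 8.851.

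| Reading of the inputs | Quantiles | n per group | By t distribution |
|---|---|---|---|
| Two-sided 0.05, β 0.2 | 1.960 + 0.842 | 69.5, so 70 | 71 |
| One-sided 0.05, β 0.2 | 1.645 + 0.842 | 54.7, so 55 | 56 |

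Neither gives 76, and rounding does not bridge the gap.

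**Step 2: the hypotheses as printed.** With a margin in the null, the denominator becomes (expected difference − margin)². Here that is (2.99 − 2.99)² = 0, so no finite n exists. If the true difference is 2.99, the power of that test equals α whatever the sample size.

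**Step 3: what does give 76.** One-sided α 0.05 with the 0.90 quantile: 8.851 × (1.645 + 1.282)² = 75.8, so 76. This arises from β = 0.10, or from a formula that takes β/2 = 0.10, as equivalence-type formulas do. The second route leaves all five printed parameters unchanged. The article does not show which function was run.

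**Step 4: the loss allowance.**
- Published: 91 per group. 76 × 1.2 = 91.2, which matches. The article shows no operation, so the multiplier is inferred.
- Remaining after 20% loss: 91 × 0.8 = 72.8, about 73.
- Needed to keep 76: 76 / (1 − 0.20) = 95 per group, 190 in total.
- 91 per group keeps 76 only if loss is 1 − 76/91 = 16.5%.

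**Step 5: the power delivered against zero difference**, at difference 2.99 and SD 6.29.

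| n per group | Two-sided, normal | Two-sided, t | One-sided, normal | One-sided, t |
|---|---|---|---|---|
| 73 | 81.9% | 81.4% | 89.0% | 88.8% |
| 76 | 83.4% | 82.9% | 90.1% | 89.8% |

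**Step 6: recruitment needed for the recomputed n.** 71 / 0.8 = 88.75, so 89 per group (178 in total); 56 / 0.8 = 70 per group (140 in total). Both lie below 182.

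**The case against.** The strongest reply is that nothing is lost. For a zero-difference null, the two slips together still leave the trial above its 80% target, and 182 is more than the inputs require. That stands. A reader might infer from the shortfall of about 3 per group that the trial is underpowered. The documents do not support that: 73 falls short of the protocol's own 76, but exceeds the 71 or 56 that the inputs require.

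A reader might also infer that 76 came from an undisclosed SD or difference. Solving backwards two-sided, a difference of about 2.86 or an SD of about 6.58 would produce it. Neither value appears in the article, and the route through the 0.90 quantile reaches 76 with the printed SD and difference. A different power term is therefore the simpler explanation, though not a proven one.

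It would likewise go too far to call 71 the single correct number. The article does not say two-sided, and its hypotheses are one-directional, so 56 is equally open until sidedness is stated.

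Finally, sections {18b} and {20c} keep every randomised participant in the analysis, with multiple imputation, so 73 is not strictly the planned analysis set. This softens the point but does not remove it. Imputation does not restore all the lost information, and the protocol itself inflates for loss, which treats 76 as the number needed after loss.

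**Conclusion.** The point holds as a correction to stated figures. The published 76 is not what the named superiority formula gives from the stated inputs: it is 5 above the two-sided t-based 71 and 20 above the one-sided t-based 56. On the hypotheses as printed, no sample size follows at all. The published 91 falls 4 per group short of the 95 needed to keep 76 at 20% loss, and leaves about 73.

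No loss of power below 80% is shown for a test against zero difference: about 81% two-sided or about 89% one-sided with 73 per group. Those figures assume the stated SD of 6.29, a true difference of 2.99, and 20% loss treated as lost information. They do not apply to a test against a non-zero margin. That 76 came from the 0.90 quantile and 91 from × 1.2 are inferences from matching numbers.

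**What to change.** Keep 182 and rewrite the end of Sample size {14}:

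- State whether α is one- or two-sided.
- State the null value actually tested: zero difference, or a margin distinct from the expected difference. Use separate symbols for the two, and bring the printed hypotheses into line.
- State the formula or function used. Check first whether it took β/2 or β 0.10 in place of the stated 0.2.
- Replace 76 with the number that results: for a zero-difference null, 71 per group (two-sided t test) or 56 (one-sided t test).
- State that 91 randomised per group with 20% loss leaves about 73, and that this gives about 81% power two-sided (about 89% one-sided) against zero difference.

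If a non-zero margin is kept, the number has to be recomputed from the expected difference minus that margin, and the support for 182 reassessed on that basis.

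For a zero-difference null, the cost is a few sentences and no extra participants. Section {25} lists changes to the sample size calculations among those needing a formal amendment to the ethics committee, so the rewrite should go through that route.

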### Recruitment {15}

The SBIRT program will be the primary recruitment source. Annually, this program detects roughly 60 people looking for treatment for AUD in each PC center. Working in close coordination with the local SBIRT program administrator, an RA will contact these individuals and invite them to participate in the study. Also, the clinical staff in the center will be able to refer potential participants to the study.

In case participant enrolment is slow, we will advertise the study in the community.

## Assignment of interventions: allocation

### Sequence generation {16a}

Participants will be randomly assigned to either control or experimental group with 1:1 allocation as per a computer-generated randomization schedule stratified by site and the baseline SDSS-DAYS score using permuted blocks of random sizes. The cut point for the severity score will be determined during the trial pilot. To ensure concealment, we specified the block sizes in a separate document with restricted access.

### Concealment mechanism {16b}

An online, central randomization service will randomize the participants to either group. This service assures concealment since it only reveals the sequence after the completion of baseline measurements and the confirmation of eligibility.

### Implementation {16c}

During the intake visit, an RA will first administer the baseline measurements, then check the inclusion/exclusion criteria, and finally, ask the central randomization service to assign the participant. The RA will use an online platform to complete the assessments and the randomization.

## Assignment of interventions: blinding

### Who will be blinded {17a}

An RA blinded to the allocation of the participant will perform the follow-up assessments. Due to the nature of the intervention, the participants and the therapists will know in which group they are participating; however, they will be strongly instructed to not disclose their allocation at the follow-up assessments. At trial closure, a statistician blinded to allocation will conduct the data analysis.

### Procedure for unblinding if needed {17b}

Not applicable since both participants and therapists are not blinded, and any undesired effects of the intervention will be managed without the need for unblinding.

## Data collection and management

### Plans for assessment and collection of outcomes {18a}

#### Primary outcome

The DDD during the last 90 days will be obtained using the Timeline Follow Back [33] (TLFB) procedure. The TLFB uses a calendar with key dates as memory aids to enhance recall. This method will also record other treatments that the participants received and capture the alcohol use pattern, which is defined as the typical number of drinks consumed in a drinking occasion in the previous 90 days, the frequency of heavy drinking days during the last 90 days (> 4 standard drinks in women and > 5 in men), and the total number of standard drinks consumed in a week during the last 90 days. The reliability of these measurements using TLFB lies between 0.7 and 0.9 [33].

##### Drinker Inventory of Consequences (DrInC-2R)

This inventory addresses the negative consequences of alcohol abuse during the last 3 months using five sub-scales: physical, interpersonal, intrapersonal, social responsibility, and impulse control. Its global score ranges from 0 to 150, with higher scores indicating higher consequences. The test-retest reliability for total consequences is 0.88 (ICC), and the sub-scales range from 0.69 to 0.92 (ICC) [36]. Even though the reduction of repercussions is at the heart of treatment objectives, we did not choose it as the primary outcome because it is harder to measure and less sensitive in the short-term. This inventory will be completed by the participant with the supervision and assistance of the RAs.

##### SOCRATES

This 19-item scale measures the motivation in a continuum of three main sub-scales [taking steps (score range 8–40), recognition (7–35), and ambivalence (4–20)] that explain 45% of the variance and have good internal consistency (Cronbach’s alphas between 0.87 and 0.96), with excellent test-retest properties (interclass correlations ranged from 0.82 to 0.94) [37]. This scale will be completed by the participant with the supervision and assistance of the RAs.

##### Outcome adjudicators

In this study, the RAs will be a small group of health professionals (i.e., nurses, psychologists, or social workers) who have experience in mental health in PC and who will complete a training program to standardize data collection procedures and ensure the skillful application of the psychometric instruments according to the test manuals.

### Plans to promote participant retention and complete follow-up {18b}

To minimize participant’s burden in the process of data collection, they will receive economic compensation for attending the two follow-up sessions. Furthermore, to reduce attrition and maximize completeness of data, we have put special care in keeping the data to the minimum necessary for the trial objectives.

To encourage attendance to therapy and follow-up sessions, a centralized appointment and reminder system will contact the participants in advance.

Despite these strategies, it is anticipated that some participants will not adhere to the follow-up schedule, the therapeutic scheme, or other crucial aspects of the protocol; however, we will include all participants in the analysis to be consistent with an intention-to-treat approach.

### Data management {19}

In this trial, all data will be entered electronically at the site where data originated using a tablet computer. Customary verification algorithms will ensure completeness and validity at the moment of data entry. There will not be any paper copies of the psychometric instruments or the demographic data forms other than what is required for the treatment sessions (i.e., structured feedback). These procedures avoid data transcription and ensure the integrity from the moment of collection. The database will be stored in a private server and will be backed-up weekly.

### Confidentiality {27}

Data will be anonymized to ensure confidentiality through a unique participant number that will link the electronic data with the participant’s identification. The informed consent document will be the only record containing both the identification number and the participant’s personal information. This document will be stored in a secure place at each site and transferred monthly to the central coordinating center, where it will be stored for 5 years after study closure. A formal presentation to the Ethics committee is necessary to access these documents.

### Plans for collection, laboratory evaluation, and storage of biological specimens for genetic or molecular analysis in this trial/future use {33}

Not applicable as no biological specimens will be collected as part of this trial.

## Statistical methods

### Statistical methods for primary and secondary outcomes {20a}

We will compare the BMT group with the EUC group for every main outcome listed in Table 1. *T* tests will compare continuous results, and chi-squared tests will compare dichotomous outcomes. We will compute mean differences (MD) for continuous outcomes, and relative risks (RR) and RR reductions (RRR) for dichotomous results, with their corresponding 95% confidence interval. *P* values will be reported to four decimal places, with *P* values less than 0.001 reported as < 0.001. The latest version of R [31] will be used to perform the statistics. Table 1 summarizes the methods for the analysis of each outcome.

**Table 1 Tab1:** Statistical methods for outcomes and ancillary analyses

Outcome	Hypothesis	Outcome measure	Methods of analysis

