### Outcomes {12}

#### Primary outcome

The primary outcome is the change from baseline in the drinks per drinking day (DDD) during the last 90 days (i.e., the previous 12 weeks), measured at 6 months follow-up. The DDD will be aggregated using means.

The DDD constitutes a relevant outcome because the frequency and quantity in which alcohol is consumed mediate the occurrence of behavioral disorders and health deterioration in clients with AUD. Even though a more comprehensive result, such as clinical recovery or improved quality of life, would be of more clinical significance, these outcomes exceed a short-term, exploratory trial. We have chosen DDD because it has shown to be sensitive to treatment and because it allows comparability with influential clinical trials [21].

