**1) Primary**			
a) Drinks per drinking day at 6 months	BMT reduced outcome from baseline to 6 months	Drinks per drinking day during the last 90 days in the Timeline Follow Back [continuous]	*T* test

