**4) Sensitivity analyses**			
a) Per-protocol analysis			a) *T* test/chi-squared
b) Adjustment for baseline variables			b) Linear model (multivariate regression)
c) Missing data imputation			c) Multiple imputation (missing-at-random assumption)

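### The primary t test is unadjusted although randomisation is stratified and baseline DDD is collected; it is valid but inefficient, and the protocol leaves open whether it tests change or the 6-month level

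*Protocol article*

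**What the plan says.** - **Test.** The section on statistical methods for primary and secondary outcomes {20a} states that t "tests will compare continuous results, and chi-squared tests will compare dichotomous outcomes". It makes the comparison between the two arms. Table 1 lists a t test for the primary outcome and names no covariates.
- **Randomisation.** Sequence generation {16a} has the schedule "stratified by site and the baseline SDSS-DAYS score using permuted blocks of random sizes". Implementation {16c} places the baseline measurements before allocation.
- **Endpoint.** The Outcomes section {12} says "The primary outcome is the change from baseline in the drinks per drinking day (DDD) during the last 90 days", assessed at 6 months. Table 1 labels the outcome as DDD at 6 months, its measure column does not mention change, and its hypothesis reads "BMT reduced outcome from baseline to 6 months".
- **Planning.** Sample size {14} compares expected levels of 9.89 and 6.9 DDD. It takes its SD from Project MATCH, which "observed a standard deviation (SD) of 6.29 drinks". No SD of change and no correlation between baseline and follow-up is given.
- **Adjustment.** It appears only as sensitivity analysis 4b in Table 1: "Linear model (multivariate regression)".

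**The concern.** Two things meet here.

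First, the primary comparison leaves out the variables most likely to explain outcome variance: baseline DDD, and the two factors used to balance the arms. If strata that predict outcome are balanced by design but ignored in the analysis, their variance stays in the error term and the standard error is too large.

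Second, the analysed variable is not fixed. If the t test is run on change, as the Outcomes section implies, its SD depends on a correlation that the protocol does not give, and 6.29 is the right figure only at one value of it. If it is run on the 6-month level, as Table 1 can be read, 6.29 fits, but the declared outcome is not the one tested.

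At stake are power and precision on the main question, with at most 91 per arm recruited.

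**Working it through.** **Inputs from Sample size {14}:** SD 6.29; difference 9.89 − 6.90 = 2.99; alpha 0.05 (sidedness not stated with the parameters; hypotheses written one-sided); beta 0.2; 76 per arm, raised to 91 for 20% loss. Completers: 91 × 0.8 = 72.8, taken as 73.

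**Assumptions, not in the protocol:** the same SD at baseline and 6 months; correlation ρ between the two of 0.2 to 0.5; a test against a zero difference.

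**The plan's own figure.** n per arm = 2 × [6.29 × (z_α + z_β) / 2.99]² = 8.851 × (z_α + z_β)².
- One-sided 5%, 80% power: 8.851 × 6.183 = 54.7, so 55.
- Two-sided 5%, 80% power: 8.851 × 7.849 = 69.5, so 70.
- One-sided 5%, 90% power: 8.851 × 8.564 = 75.8, so 76.

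The stated 76 therefore does not follow from the stated beta. That is a separate matter. Here it means that 80% is not a firm starting point: with SD 6.29 and 76 per arm, power is already about 83% two-sided or 90% one-sided.

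**SD under each analysis**
- t test on the 6-month level: 6.29.
- t test on change: 6.29 × √(2(1 − ρ)), equal to 6.29 only at ρ = 0.5.
- Linear model with baseline DDD (ANCOVA): 6.29 × √(1 − ρ²).

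The ratio of ANCOVA to change-score variance is (1 − ρ²) / (2(1 − ρ)) = (1 + ρ)/2, that is 0.60 to 0.75 over this range.

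**Power, noncentral t, 73 per arm** (the few degrees of freedom spent on covariates are ignored)

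| ρ | SD change | SD ANCOVA | Two-sided 5%: change / level / ANCOVA | One-sided 5%: change / level / ANCOVA |
|---|---|---|---|---|
| 0.2 | 7.96 | 6.16 | 62 / 81 / 83% | 73 / 89 / 90% |
| 0.3 | 7.44 | 6.00 | 67 / 81 / 85% | 78 / 89 / 91% |
| 0.4 | 6.89 | 5.76 | 74 / 81 / 88% | 83 / 89 / 93% |
| 0.5 | 6.29 | 5.45 | 81 / 81 / 91% | 89 / 89 / 95% |

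**Correlation at which the change-score t test reaches 80% power**
- Two-sided 5%: 0.48 with 73 per arm, 0.46 with 76.
- One-sided 5%: 0.34 with 73 per arm, 0.31 with 76.

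**Gain from baseline adjustment, two-sided, ρ = 0.2 to 0.5**
- Over the level t test: 82.9 − 81.4 = 1.5 points up to 90.9 − 81.4 = 9.5 points.
- Over the change-score t test: 82.9 − 61.6 = 21.3 points down to 90.9 − 81.4 = 9.5 points.

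Any further gain from site and severity is not included, because the protocol gives no figures for it.

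**The case against.** The best defence is that nothing here is invalid. A t test after stratified randomisation is unbiased and, if anything, conservative, and the adjusted model is already planned as a check. That stands: this is a matter of efficiency and clarity, not of error control.

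Four stronger readings are tempting, and the protocol does not support them.

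- **That 80% power requires a correlation of about 0.5.** This needs both a two-sided test and a change-score analysis. The hypotheses introduced by "The following two hypotheses correspond to the superiority test" are one-sided, which lowers the requirement to 0.31-0.34. If the test is on the 6-month level, the condition disappears. All randomised participants are to be included, with multiple imputation. If all 91 per arm carried full information, the change-score threshold would be about 0.35 two-sided or 0.17 one-sided; imputation does not recover that much.
- **That several estimands are in play.** Under randomisation, the between-arm difference in change and in level target the same quantity. The Table 1 hypothesis sounds like a within-arm claim, but section {20a} makes the comparison between arms. The conflict is in the endpoint definition and the SD that goes with it.
- **That the protocol itself predicts large site differences in drinking.** The section on choice of comparators {6b} speaks of variability in services, and then argues that most cases will form a homogeneous cohort.
- **That the gain is always large.** Against a t test on the level it is modest, especially at low correlation.

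It is also fair to say that the protocol does not state when the 6.29 was measured, and that equal SDs at both times may not hold when means are expected to fall.

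**Conclusion.** The point holds as a recommended improvement. The protocol fixes an unadjusted t test for its primary outcome, puts the adjusted model among the sensitivity analyses, and does not settle whether change or the 6-month level is analysed.

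Under the assumptions above, the choice costs about 1.5 to 9.5 percentage points of power if the test is on the level, and about 10 to 21 points if it is on change (two-sided 5%). Baseline adjustment is more powerful than the change-score test at every correlation below 1, whichever sidedness applies. The exact size depends on a correlation that the protocol does not give.

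The figures apply to a test against zero. The sample size of 76 that cannot be reproduced, and the superiority margin set equal to the expected difference, are separate problems that this change does not address.

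**What to change.** - Make the primary analysis a linear model of 6-month DDD on arm, baseline DDD, baseline SDSS-DAYS (or its randomisation stratum) and site, pooling very small sites. Report the adjusted mean difference with its 95% confidence interval.
- State in both the Outcomes section and Table 1 that this is the primary analysis. With baseline DDD in the model, the treatment estimate is the same whether the response is the level or the change, so the two places then agree.
- Use the same model for the continuous secondary outcomes, each with its own baseline value where one is measured.
- Keep the unadjusted t test as a supportive analysis.
- State the sidedness of the test and, if power is quoted again, the assumed correlation.

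The cost is wording, submitted as an amendment because the protocol treats changes to the statistical analysis that way. No new data are needed: baseline DDD, severity and site are already recorded, and linear models are already planned for the sensitivity and subgroup analyses.
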